#### Plans to promote participant retention and to complete follow-up

There are no additional strategies to promote participant retention since follow-up is the standard of care. In cases where the participant withdraws informed consent, only previously collected data will be used for this study.

#### Data management

Data will be managed by local investigators and local data managers, and local supporting researchers/research assistants. using the online data management system ‘Research Manager’ [45]. Each patient receives a unique study number generated by the data management system. The study number is linked to patient details and is stored in a password-secured file that can only be accessed by the research investigators.

#### Confidentiality

All analyses of study data during the trial period will be carried out in compliance with the relevant regulations for data protection. Personal identifiers will be replaced by a study number generated in ‘Research Manager’. The study data is only accessible by the investigators. Research data that needs to be taken away from the research center will not contain any personal information of the participants. If necessary, government regulatory authorities or ethics committees may access patient data from the study. At the end of the trial, permission from the participants for further storage or for the use of any specimens is already available, since this is included in the signed informed consent form (Additional file 2). Finally, the study results will be published with non-identifiable personal data once the trial has ended.

#### Additional consent provisions for the collection and use of participant data and biological specimens

The collection, processing, and storing of biological specimens will be carried out in accordance with the applicable institutional policies. The use of specimens is described in the patient’s informed consent form (Additional file 2).

### Statistical methods

#### General statistical analysis

Categorical variables will generally be presented as numbers (frequencies) and percentages. Continuous variables will be presented as the mean and standard deviation, or as the median and interquartile range in case of a skewed distribution. The data will only be analyzed and presented quantitatively. Missing data will not be replaced.

#### Statistical analysis of the primary study parameters

For each group, the number of patients who are alive and without evidence of disease relapse after 3 years of follow-up will be determined. Kaplan–Meier curves with the end-point of disease-free survival will be constructed and the log-rank test will be used to compare 3-year disease-free survival rates between groups.

In the case of differences in baseline variables between the two groups, Cox regression analyses including these variables will be performed. Univariate analysis will first be used to identify possible confounders. Multivariate Cox regression analysis will then be performed including ‘group’ (PSO or no PSO), with possible confounders as independent variables and disease-free survival as the dependent variable.

The NNT to prevent one case of ovarian cancer will be calculated according to the method of Lubsen et al*.* [35]. NNT describes the number of patients required to undergo PSO in order to gain 1 year of disease-free survival.

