**Primary**		
Occurrence of ovarian cancer (primary or metastatic)	Incidence	36 months
Number needed to treat to prevent one case of ovarian cancer (primary or metastatic)	NNT	36 months

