### Primary objective

The main aim of this study is to determine whether prophylactic bilateral salpingo-oophorectomy conducted in postmenopausal patients aged ≥60 years during surgery for primary CRC reduces the incidence of ovarian malignancies (metastatic or primary) during a three-year follow-up period. Moreover, this study will provide the data necessary to calculate the number needed to treat (NNT) in order to prevent one case of ovarian cancer (metastatic or primary).

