### Secondary objectives

• What is the effect of PSO on disease-free survival (DFS) after 3-years of follow-up? What is the concomitant NNT to gain one year of DFS, according to the method of Lubsen *et al.* [35]?• What is the effect of PSO on surgery-related morbidity?• In the non-PSO group, what is the incidence and pattern of intra-abdominal relapse, including CRC ovarian metastases and primary ovarian cancer, requiring renewed surgical intervention?• During primary surgery, how often are abnormal ovaries found that require resection?• What is the incidence of (micro)metastatic disease in the ovaries of patients with primary CRC?• What is the effect of PSO on quality of life as assessed using health-related quality of life (HRQL) questionnaires, and effects such as surgery for abdominal adhesions occurring within 3 years?• What is the effect of PSO on 5-year overall survival?• What is the percentage of patients who have a preference for PSO (or no PSO) when scheduled for surgery for primary CRC? Within 3 years of their index surgery, how many patients revise their initial decision of no PSO and subsequently undergo PSO?• Are there differences in the baseline characteristics between patients who choose PSO compared to those who do not? (The baseline patient characteristics include age, ASA-classification, BMI, previous unilateral oophorectomy, comorbidities, and neo-adjuvant therapy (Table 2))

**Table 2 Tab2:** Baseline characteristics of study patients

Baseline characteristic	PSO	Non-PSO
Age, mean (SD) or median (IQR), years		
ASA classification, No. (%)		
ASA-1		
ASA-2		
ASA-3		
ASA-4		
BMI, mean (SD), median (IQR), kg/m^2^		
Previous (unilateral) oophorectomy		
Yes, unilateral		
Yes, bilateral		
No		
Comorbidities, No. (%)		
Smoking (yes/no)		
Chronic pulmonary disease (yes/no)		
Hypertension (yes/no)		
Diabetes mellitus (yes/no)		
Myocardial infarction (yes/no)		
Transient ischemic attack (yes/no)		
Cerebral vascular accident (yes/no)		
Central arterial disease (yes/no)		
Peripheral arterial disease (yes/no)		
Severe kidney disease (GFR < 30 mg/mmol) (yes/no)		
Neo-adjuvant therapy		
No		
Yes, chemotherapy		
Yes, radiotherapy		
Yes, chemoradiotherapy		

*SD* standard deviation, *IQR* interquartile range, *y* year, *ASA* American society of anesthesiologists, *no* number, *BMI* body mass index, *GFR* glomerular filtration rate

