### Sample size

The primary study outcome is the occurrence of either CRC metastases in the ovaries or primary ovarian cancer within 3 years after resection of the (primary) colorectal tumor. Based on previous studies, we assume the incidence of synchronous and metachronous colorectal metastases in the ovaries will be 2.0% during the follow-up period [15, 17, 21]. The incidence of primary ovarian cancer is expected to be 0.1% in this period [39]. This gives an overall incidence of 2.1% in cases where PSO is not performed (non-PSO group).

Following PSO, colorectal tumors can no longer metastasize to the ovaries, while the incidence of primary ovarian malignancy should presumably be 0% (PSO group). However, a small risk of primary ovarian malignancy still exists after PSO due to the development of ‘ovarian remnant syndrome’ (ORS) [40–42]. This risk is estimated to be approximately 0.01% for the PSO group.

Based on these assumptions and an alfa of 0.05 with power of 80%, a sample size calculation was performed using an online sample size calculator for comparison of two proportions [43]. This gave a sample size of 371 patients per group, or 742 in total.

Since all eligible patients are not randomized, it is necessary to correct for possible confounders. According to the one-in-ten rule, at least 10 events (of ovarian malignancies) are needed per factor studied in order to achieve sufficient statistical power [44]. Besides PSO, correction will also be made for age as another possible confounder.

Based on current clinical practice, we estimate that about half of all postmenopausal CRC patients undergo PSO during resection of their colorectal tumor. Therefore, we expect the two study groups to be approximately equal in size. The estimated incidence of ovarian malignancies in the total study population will thus be 1.055% (average of 2.1% and 0.01%), thus requiring a sample size of at least 1896 patients (20/0.01055).

Finally, after taking into account a dropout rate of 5%, at least 1996 patients should be recruited into the study.

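### The primary analysis section tests disease-free survival, a secondary outcome; the primary outcome that sized the study, ovarian malignancy at 36 months, has no specified between-group analysis.

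*Protocol article*

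**What the plan says.** Four places in the protocol article agree on the primary outcome.

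- The abstract names the reduction in ovarian malignancies, and the corresponding NNT, as the main study parameters.
- Table 1 lists the occurrence of ovarian cancer, primary or metastatic, at 36 months under Primary.
- The Primary objective asks whether PSO "reduces the incidence of ovarian malignancies (metastatic or primary) during a three-year follow-up period".
- The Sample size section states: "The primary study outcome is the occurrence of either CRC metastases in the ovaries or primary ovarian cancer within 3 years after resection".

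DFS is secondary, both in Table 1 and under Secondary objectives: "What is the effect of PSO on disease-free survival (DFS) after 3-years of follow-up".

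The section Statistical analysis of the primary study parameters then turns to DFS. It counts patients alive without relapse at 3 years and specifies a Kaplan–Meier analysis: "end-point of disease-free survival will be constructed and the log-rank test will be used to compare 3-year disease-free survival rates between groups". The adjusted model is a Cox regression "with possible confounders as independent variables and disease-free survival as the dependent variable". The section closes with an NNT: "The NNT to prevent one case of ovarian cancer will be calculated according to the method of Lubsen et al". The next sentence, however, defines that NNT as the number of patients who must undergo PSO to gain one year of DFS, which is the quantity listed under Secondary objectives.

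**The concern.** The section that should analyse the primary outcome analyses a different one. A statistician following it would report a DFS log-rank test and a DFS Cox model as the primary result, with nothing specified to answer whether PSO reduces ovarian malignancy.

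This matters for three reasons. First, ovarian events are a small part of all relapses and deaths, so a real effect on them is heavily diluted in DFS. A null DFS result could be read as no benefit from PSO even if ovarian malignancies were almost eliminated. Second, groups form by patient preference and the Sample size section calls confounder correction necessary, yet under the primary heading adjustment is specified only for DFS. Third, two competing candidates for the primary analysis leave room to choose between them after the data are seen.

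**Working it through.** **Which outcome the sample size belongs to**

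Inputs, all from Sample size: 2.1% without PSO (2.0% metastases plus 0.1% primary ovarian cancer), 0.01% with PSO, alpha 0.05 (taken as two-sided), power 80%, groups of about equal size, 10 events for each of two factors (PSO and age), 5% dropout.

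- Two proportions, unpooled variance: n = (1.960 + 0.842)² × [0.021 × 0.979 + 0.0001 × 0.9999] / (0.021 − 0.0001)² = 371.2 per group. The protocol states 371. The pooled version gives 374.
- Events rule: 20 / 0.01055 = 1895.7, so 1896, as stated.
- Dropout: 1896 / 0.95 = 1995.8, so 1996, as stated.

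Every sizing figure reproduces, and every one rests on ovarian malignancy rates. DFS does not enter.

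**Power for the outcome defined as primary**

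With 1896 / 2 = 948 per group, expected events are 948 × 0.021 = 19.9 without PSO and 948 × 0.0001 = 0.1 with PSO. Power is 99.4% by the two-proportion normal approximation and 99.98% by Fisher's exact test. The implied NNT is 1 / (0.021 − 0.0001), about 48.

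**Power for the outcome tested under the primary heading**

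Suppose PSO affects DFS only by removing ovarian malignancies. The 3-year DFS gain is then at most 2.1 − 0.01 = 2.09 points. The protocol gives no 3-year DFS for this population, so the baselines below are assumptions. The 68% is the 5-year control-group figure from the randomised study cited in the introduction.

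Hazard ratio = ln(DFS with PSO) / ln(DFS without PSO). Events = 948 × the sum of the two event risks. Schoenfeld power = Φ(√events / 2 × |ln HR| − 1.96). The last column is the number for a two-proportion comparison at 3 years.

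| Assumed 3-year DFS without PSO | HR | Events | Log-rank power | Per group for 80% power |
|---|---|---|---|---|
| 85% | 0.851 | 265 | 26% | 4315 |
| 80% | 0.884 | 359 | 21% | 5520 |
| 75% | 0.904 | 454 | 19% | 6546 |
| 70% | 0.918 | 549 | 17% | 7392 |
| 68% | 0.922 | 587 | 17% | 7680 |
| 60% | 0.933 | 739 | 15–16% | 8545 |

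**Whether the composite is compared elsewhere**

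Statistical analysis of secondary study parameters compares intra-abdominal relapse, which is broader than ovarian metastasis, and primary ovarian cancer as separate outcomes. Primary ovarian cancer is 0.1 of the assumed 2.1 points: 948 × (0.001 + 0.0001), or about one expected event in the whole study. The same section says metastatic spread to the ovaries on pathology cannot be compared between groups. No section specifies a test, model or interval for the composite.

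**The case against.** The strongest objection is that a between-group analysis of the composite is implied. The Sample size section uses a two-proportion comparison, counts ovarian malignancies towards the events rule and promises adjustment for age. Table 1 still requires incidence and NNT at 36 months, so these would be reported beside DFS, and an analysis plan or fuller protocol may exist. This shows what was probably intended. It does not remove the contradiction: the protocol is not silent but names another endpoint under the primary heading, and puts even the NNT on the DFS scale.

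Four narrower objections have weight.

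- **The power figures are conditional.** Consequences of PSO lists reduced recurrence as a separate proposed benefit. If PSO raised 3-year DFS from 70% to 75%, the same formula gives about 69% power; from 68% to 78%, the non-significant 5-year contrast in the cited randomised study, over 99%. The low figures hold only if PSO acts solely through ovarian events.
- **The pathology sentence** most naturally concerns (micro)metastases in resected ovaries. It does not rule out comparing ovarian metastases detected during follow-up, so it should not carry the argument.
- **Whether a new primary ovarian cancer counts as a DFS event** is unclear, because the section speaks of disease relapse. The rationale for PSO implies that it counts. Only 0.1 of the 2.1 points is involved.
- **The 0.01% rate may be optimistic.** The 2.0% includes synchronous metastases, and occult ones could be found in PSO specimens. The power for the composite depends on how these are counted.

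None of these changes which endpoint the primary section tests.

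**Conclusion.** The concern holds and must be fixed. The protocol defines and sizes one primary outcome and specifies the primary analysis of another; the composite ovarian outcome has no specified group comparison. This follows from the text alone, without any power assumption.

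On the protocol's rates, 948 per group give over 99% power for ovarian malignancy. The DFS test has about 15% to 26%, given an assumed baseline 3-year DFS of 60% to 85% and an effect of PSO only through ovarian events. A wider effect on DFS would raise that power, but the stated 80% would still not be a property of the DFS test.

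**What to change.** In Statistical analysis of the primary study parameters:

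1. Make the primary analysis the between-group difference in 36-month cumulative incidence of ovarian malignancy (metastatic or primary), with index surgery as time zero and a 95% confidence interval.
2. Adjust for age, as the Sample size section plans. With about 20 events expected against 0.1, ordinary regression will be close to separation, so name a method suited to sparse events, such as Firth-penalised or exact methods. If more confounders are to enter, reconcile that with the two-factor events rule.
3. Derive the primary NNT from this risk difference. Keep the NNT per year of DFS as a secondary quantity under its own name.
4. State whether ovarian metastases found at index surgery or in PSO specimens count as primary events.
5. Move the DFS Kaplan–Meier, log-rank and Cox analyses to the secondary section, say whether a new primary ovarian cancer is a DFS event, and state that the sample size does not power DFS.

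The cost is wording in the protocol and any analysis plan. No sample size figure changes, and no new patients or data are needed.

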### Other study parameters

Other information will be collected on the type of surgery (colon *vs* rectum, laparoscopic *vs* open), operative duration, intraoperative blood loss, adjuvant treatment strategies, and pTNM classification. Preoperative data are collected during admission to the surgical and/or gynecology department. Data collected during operation is noted in the operative report. Quality of life after the operation is evaluated by questionnaires (part of the standard follow-up / value-based healthcare) given at 3 months and at 1-, 2- and 3-year(s) after surgery. Data collection is performed centrally.

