#### Other study parameters and methods for additional analyses

All baseline parameters will be compared between groups using either chi-square tests for categorical variables and t-tests, or Mann–Whitney U-tests for continuous variables.

In addition, the surgical substrate (colon *vs* rectum), type of surgery (laparoscopic *vs* open) and use of adjuvant treatment are compared between groups using chi-square tests.

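### The DFS adjustment rule depends on baseline differences and univariate screening of a list without tumour stage or site, so stage can be left out of the comparison of preference-formed groups

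*Protocol article*

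**What the plan says.** All references are to the protocol article. Under Randomization, blinding and treatment allocation, the two groups are formed by patient preference.

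The rule for the DFS comparison stands under Statistical analysis of the primary study parameters:

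- The trigger: "In the case of differences in baseline variables between the two groups, Cox regression analyses including these variables will be performed".
- The screen: "Univariate analysis will first be used to identify possible confounders". No criterion is given.
- The model: a Cox regression with group, "with possible confounders as independent variables and disease-free survival as the dependent variable".

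The candidate variables have to be pieced together from other sections:

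- Secondary objectives: "The baseline patient characteristics include age, ASA-classification, BMI, previous unilateral oophorectomy, comorbidities, and neo-adjuvant therapy". Table 2 likewise has no row for tumour stage or site.
- Other study parameters: colon versus rectum is collected, as are "operative duration, intraoperative blood loss, adjuvant treatment strategies, and pTNM classification".
- The section on additional analyses shows that differences are judged by significance tests: "All baseline parameters will be compared between groups using either chi-square tests for categorical variables and t-tests, or Mann–Whitney U-tests for continuous variables". Colon versus rectum is then added as a further chi-square comparison, together with "type of surgery (laparoscopic *vs* open) and use of adjuvant treatment are compared between groups using chi-square tests". pTNM is not mentioned.

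The Sample size section says that correction for confounders is needed because patients are not randomised. It names age as the factor to be corrected for besides PSO and attaches no test to that commitment.

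**The concern.** A between-group test measures imbalance relative to sample size. It does not show whether a variable confounds. A moderate imbalance in a strongly prognostic variable can bias the result without reaching significance, and a significant imbalance in a non-prognostic variable does no harm.

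The larger problem is the list to which the rule applies. If the baseline variables are those in Table 2, stage never reaches the test, the screen or the model. The DFS hazard ratio could then be reported without adjustment for a prognostic variable that the study has collected. The Discussion expects the findings to be able to inform guidelines, so a hazard ratio that reflects case mix would matter.

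The age commitment under Sample size is unconditional, while the analysis section would adjust for age only if the groups differ or age passes the screen. Both cannot be followed.

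**Working it through.** **1. The plan's own figures.** With 2.1% versus 0.01%, two-sided alpha 0.05 and 80% power, the unpooled formula gives 371.2 per group (stated: 371). 20/0.01055 = 1895.7, so 1896. 1896/0.95 = 1995.8, so 1996. All reproduce. The steps below use 1896/2 = 948 per group.

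**2. Largest plausible DFS effect.** Suppose every avoided ovarian malignancy is also an avoided DFS event. DFS then rises by at most about 2.1 percentage points, and HR = ln(DFS in PSO)/ln(DFS in non-PSO).

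- Non-PSO DFS 70% (assumed): ln(0.721)/ln(0.70) = 0.917.
- Non-PSO DFS 75% (assumed): ln(0.771)/ln(0.75) = 0.904.
- Non-PSO DFS 68% or 78% (the two 5-year figures from the earlier randomised study cited in the Introduction): ln(0.701)/ln(0.68) = 0.921 and ln(0.801)/ln(0.78) = 0.893.

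**3. Bias if stage is never a candidate.** For a binary feature with hazard ratio H, the unadjusted group hazard ratio is multiplied by about [1 + p(PSO)(H − 1)]/[1 + p(non-PSO)(H − 1)]. Assume 15% in PSO and 25% in non-PSO.

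- H = 2: 1.15/1.25 = 0.92.
- H = 3: 1.30/1.50 = 0.87.

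These match or exceed the whole effect in step 2.

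**4. Simulation.** 300 runs per scenario, 948 per group, no true PSO effect, non-PSO DFS 68% at 3 years, 35% advanced stage in non-PSO, stage HR 3 (all assumed). The stage imbalance is fewer advanced cases in PSO.

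| Stage imbalance | HR, stage omitted | False positives, stage omitted | HR, stage forced in | False positives, stage forced in | False positives, adjust only if chi-square p < 0.05 |
|---|---|---|---|---|---|
| 0 points | 1.005 | 4.7% | 1.004 | 4.3% | 4.3% |
| 4 points | 0.953 | 8.7% | 0.998 | 5.0% | 4.0% |
| 8 points | 0.909 | 18.0% | 0.997 | 6.0% | 6.0% |

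The formula in step 3 agrees: (1 + 0.31 × 2)/(1 + 0.35 × 2) = 1.62/1.70 = 0.953 for 4 points, and 1.54/1.70 = 0.906 for 8 points.

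**5. What testing would miss if stage were a candidate.** At 35% prevalence, the largest non-significant difference is about 1.96 × √(2 × 0.35 × 0.65/948) = 4.3 points. A 4-point imbalance is flagged with probability 0.457, so it is missed about 54% of the time, with an HR of about 0.97 (stage HR 2) to 0.95 (stage HR 3). An 8-point imbalance is flagged about 96% of the time. For 25% versus 15%, z ≈ 0.10/√(2 × 0.20 × 0.80/948) = 5.4, so it would nearly always be flagged.

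**6. Room in the models.** As a gauge, the cited 5-year DFS figures give 1896 × 0.22 = 417 to 1896 × 0.32 = 607 DFS events, or 41 to 60 factors at ten events each; the 3-year count may be lower. The ovarian endpoint expects 948 × 0.021 = 19.9 events in non-PSO and 948 × 0.0001 = 0.1 in PSO, which is two factors under the plan's own rule.

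**The case against.** **The primary outcome is not at risk in this way.** Table 1 and the Sample size section make ovarian malignancy the primary outcome, at 2.1% versus 0.01%, a ratio of about 200. A reader might infer that confounding could imitate the primary effect. A bias factor of 0.87 to 0.92 could not. This stands: the size applies to DFS only, which Table 1 lists as secondary although the primary analysis section is built on it.

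**P-value screening alone does limited damage.** A reader might take it to be as harmful as omitting stage. Steps 4 and 5 do not support that. A 25% versus 15% imbalance would nearly always be caught if stage were tested, and test-then-adjust kept false positives at 4–6%. This stands too: the main harm is that stage need not be a candidate, and the selection rule adds a smaller bias.

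**The list may be open.** The baseline list is introduced as inclusive rather than exhaustive, and the confounders are not expressly limited to Table 2. Site is compared between groups and could be carried forward. Neo-adjuvant therapy may carry some stage and site information. A final covariate list is often left to the full protocol or SAP. This weakens the case for site more than for stage. It does not rescue the rule, which is stated, and nothing commits to adjusting for stage.

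**The pathway is assumed.** The documents do not say that stage or site is the strongest predictor of relapse or that it affects the choice. Patients are approached before surgery, when pathological stage is unknown, so only clinical stage could influence them. The point needs only that stage is prognostic and may differ between self-selected groups.

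**Conclusion.** The point holds for the DFS comparison. Followed as written, the rule can leave stage out of the Cox model, and it conflicts with the unconditional commitment to age.

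Under an assumed 25% versus 15% imbalance and a stage HR of 2 to 3, omission shifts the DFS hazard ratio by a factor of 0.92 to 0.87. The largest effect the plan's ovarian risk allows is about 0.90 to 0.92 at an assumed 70–75% DFS. The prevalences, stage hazard ratios and DFS levels are not in the documents, and neither is the direction of the imbalance. What the documents do show is that nothing in the stated rule would secure the adjustment if such an imbalance occurred. The case is firmer for stage than for site. The change is needed before the DFS result is used as evidence of benefit.

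**What to change.** - **DFS Cox model.** Replace the difference trigger and the univariate screen with one prespecified set, used whatever the baseline tests show: age, ASA class, BMI, comorbidity, neo-adjuvant therapy, tumour site, pT, pN and preoperatively known metastatic disease.
- **Exclusions.** Leave out variables that follow PSO: M status established only from the removed ovaries, adjuvant treatment, blood loss and operative time.
- **Ovarian-malignancy endpoint.** About 20 events, nearly all in one group, cannot support this set in an ordinary regression. Carry the same covariates through a propensity score or a penalised model.
- **Consistency.** Reconcile the age commitment under Sample size with the analysis section, so that both name the same set.

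The cost is protocol or SAP wording and a little more analysis work. Stage and site are already collected, and the planned sample size does not change.
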